## Abstract

**Background:**

The biopsychological response patterns to digital stress have been sparsely investigated so far. Important potential stressors in modern working environments due to increased digitalization are multitasking and work interruptions. In this study protocol, we present a protocol for a laboratory experiment, in which we will investigate the biopsychological stress response patterns to multitasking and work interruptions.

**Methods:**

In total, *N* = 192 healthy, adult participants will be assigned to six experimental conditions in a randomized order (one single-task, three dual-task (two in parallel and one as interruption), one multitasking, and one passive control condition). Salivary alpha-amylase as well as heart rate as markers for Sympathetic Nervous System Activity, heart rate variability as measure for Parasympathetic Nervous System (PNS) activity, and cortisol as measure for activity of the hypothalamic-pituitary adrenal (HPA) axis will be assessed at six time points throughout the experimental session. Furthermore, inflammatory markers (i.e., IL-6, C-reactive protein (CRP), and secretory immunoglobulin-A) will be assessed before and after the task as well as 24 hours after it (IL-6 and CRP only). Main outcomes will be the time course of these physiological stress markers. Reactivity of these measures will be compared between the experimental conditions (dual-tasking, work interruptions, and multitasking) with the control conditions (single-tasking and passive control).

**Discussion:**

With this study protocol, we present a comprehensive experiment, which will enable an extensive investigation of physiological stress-responses to multitasking and work interruptions. Our planned study will contribute to a better understanding of physiological response patterns to modern (digital) stressors. Potential risks and limitations are discussed. The findings will have important implications, especially in the context of digital health in modern working and living environments.

## Introduction

### Rationale

Stress is one important factor influencing human health [e.g., 1,2]. Stress is part of everyday private and working life, is experienced by almost everyone, and is increasingly having an impact on health and life expectancy [3,4]. In modern, technology-driven working and living environments, new potential stressors related to digitalization (i.e., digital stressors) are more and more present. In the following, we will–similar to the concepts of techno strain and technostress [5,6]–refer to stress that is related to the usage of digital technology and media as digital stress. Important potential digital stressors are multitasking and work interruptions [e.g., due to flooding text messages or emails; 7–11]. Both can be perceived as stressful and overwhelming [12–14] and cannot be avoided in many situations. However, this does not necessarily indicate that the feeling of being stressed or overwhelmed when being faced with these demands is also associated with a physiological stress response [15,16]. Although the biopsychological effects of several acute [e.g., social evaluation; 17] and chronic psychosocial stressors [e.g., caregiving; 18,19] and psychological determinants of biological stress-response patterns in general are well understood, only few attempts have been made so far to use this knowledge to understand the effects of stressors such as multitasking and work interruptions on biological stress system-activity. The aim of our planned study is to close this research gap.

The interpretation of a situation as threatening activates stress centers in the brain, which use stress systems to prepare the entire organism for dealing with the situation [20]. The Sympathetic Nervous System (SNS) activates systems throughout the body through noradrenergic innervation, which leads to the release of epinephrine and norepinephrine from the adrenal medulla and, among other things, results in an increase in heart rate and blood pressure [20,21]. The up-regulation of the SNS is accompanied by a down-regulation of the Parasympathetic Nervous System [PNS; 1,21]. The slower response of the hypothalamic-pituitary adrenal (HPA) axis modulates the effects of the SNS and PNS by releasing the stress hormone cortisol from the adrenal cortex [21,22]. With a further delay [e.g., about 1.5–2 hours for interleukin-6 (IL-6); 23,24], complex effects of the immune system are activated with up-regulation of some components (most importantly inflammatory pathways) and down-regulation of others [most importantly cellular immunity; 2,25]. Temporarily, all these physiological stress responses are adaptive. Potentially harmful consequences arise when stress becomes chronic, i.e., when long-term stress exposure occurs [e.g., 19,26–28], or when so-called maladaptive stress-response patterns are used [e.g., 29–31]. We refer to stress-responses patterns as being maladaptive–in contrast to adaptive [e.g., 32,33]–when they do not allow the organism to efficiently cope with or to adjust the individual’s physiological responses or behavior to the situation.

With regard to stress effects on health, SNS, PNS, and HPA axis interact with patho-physiologically relevant systems, of which the inflammatory system is seen–beside e.g., glucocorticoids [34]–as one key factor [35]. Inflammatory processes are one of the central mechanisms in mediating the negative effects of stress on health [35]. Ultimately, acute stress exposure leads to systemic low-grade inflammation, which is–in the long-term–a key factor for the development of the most important diseases in industrialized nations such as cardiovascular diseases, type-2 diabetes, and cancer [35,36]. Moreover, these patho-physiological stress-related processes are associated with a large number of other diseases such as chronic dermatological conditions (e.g., skin aging [37], urticaria [38,39], or skin tumors; [40]), asthma bronchiale [41,42], or obesity [43,44], and many more.

Although physiological responses can be triggered by stressors in principle, the actual stress response is associated with the nature of the stressor [so-called specificity hypothesis; 45,46]. According to this hypothesis, specifically situations that are perceived as threatening in contrast to challenging trigger HPA axis responses. Moreover, situations which are shameful or in which the social self is devaluated are associated with strong HPA responses [so-called social self-preservation theory; 47–49]. For cognitive stressors, both SNS and HPA axis responses have been reported [50,51], depending on task difficulty and on the presence of further stressors [52]. In a recent systematic review and meta-analysis from our group, which is currently under review [53], we found that SNS activity is significantly higher and PNS activity is significantly lower during dual- or multitasking than during single tasking. We identified no associations with HPA axis activity. However, the number of studies in which HPA axis reactivity to dual- or multitasking was investigated was small. We found no eligible studies in which immune system (re-) activity was investigated.

To summarize, so far, laboratory experiments in which the potential stressors multitasking and work interruptions are systematically induced are rare. Moreover, they vary in their potential how the biological stress systems are modulated and investigated. Multitasking and work interruptions differ from commonly investigated stressors in their nature as they primarily include a cognitive component in contrast to a psychosocial one, especially when induced digitally (i.e., without the presence of further persons). Therefore, with regard to the specificity hypothesis, it remains an open question whether physiological stress responses to multitasking and work interruptions differ between digital and non-digital stressors. In our planned study, we will therefore, differentiate between pure digital multitasking as well as work interruptions and comparable tasks in which another person is involved.

### Objectives

While the biopsychological effects of acute [e.g., social evaluation; 54] and chronic [e.g., caregiving; 18,19] psychosocial stressors and psychological determinants of biological stress-response patterns in general are well understood [e.g., 55,56], only few attempts have been made so far to use this knowledge to understand the effects of two prominent stressors in modern, digitalized working environments (i.e., multitasking and work interruptions) on biological stress systems. With this protocol, we present a study plan for a comprehensive experiment, in which responses of the SNS, PNS, HPA axis, as well as of the immune system to multitasking and work interruptions will be investigated in a controlled laboratory setting.

Our primary research questions are:

Do dual- and multitasking conditions lead to physiological stress responses in comparison to a single-task control condition or a passive control condition?Do work interruptions lead to physiological stress responses in comparison to a single-task control condition or a passive control condition?Do the stress response patterns differ between digital and non-digital stressors?Additionally, the following secondary research question will be investigated exploratorily:Do dual- and multitasking lead to perceived stress responses in comparison to a single-task control condition or a passive control condition?Is the physiological stress response to dual- or multitasking, or work interruptions associated with person characteristics (e.g., age, sex, body-mass-index (BMI), education) and psychological variables (e.g., personality, coping style, self-efficacy, depression, anxiety, preference for multitasking [so-called polychronicity; 57]).

Because the associations with these factors will be investigated exploratorily (i.e., without specific hypotheses), only a subset, which is known to be highly relevant in stress research (i.e., age, sex, BMI), will be considered as covariates in the statistical analyses. The actual hypotheses are specified in the Materials and Methods section below.

## Materials and methods

### Study design

The study design is a cross-sectional laboratory experiment, in which participants will be randomly assigned to one of six conditions (four experimental conditions and two control conditions; Table 1; Fig 1).

**Fig 1 pone.0263785.g001:**
[figure not shown]
Experimental conditions. Each participant will be randomly assigned to one of the six experimental conditions. In condition 5 and 6, an experimenter will be present in the same room as the participant to introduce a non-digital, social-evaluative stress component.

**Table 1 pone.0263785.t001:** Tasks that will be used in the six experimental conditions.

No.	Condition	Task 1	Task 2	Task 3
1	Passive control (digital)	Watching a non-stressful video	/	/
2	Digital single-task (active control)	Continuous-performance task	/	/
3	Dual-task with digital interruptions	Continuous-performance task	Answering questions that are digitally presented as interruptions on the same monitor	/
4	Dual-task, parallel (digital)	Continuous-performance task	Answering questions that are digitally presented in parallel on a second monitor	/
5	Dual-task, parallel (non-digital)	Continuous-performance task	Verbal-fluency task (non-digital)	/
6	Multitask, parallel dual-task with additional non-digital parallel task	Continuous-performance task	Answering questions that are digitally presented in parallel on a second monitor	Verbal-fluency task (non-digital)

### Participants

In total, *N* = 192 (32 per condition) healthy, German-speaking adults between 18 and 40 years will be recruited. Exclusion criteria are diagnosed physical or psychological disorders (operationalized as diagnosed within the last 2 years), regular medication intake (exception oral contraceptives), pregnancy, a BMI ≥ 35 kg/m^2^, regular smoking (more than 5 cigarettes per week), or being an employee of the Friedrich-Alexander University Erlangen-Nürnberg (FAU). The latter is a requirement from the workers’ council of the FAU.

### Ethics approval

The study will be conducted according to the principles expressed in the Declaration of Helsinki and has been approved by the local ethics committee of the FAU (protocol number: 397_19 B).

### Power analysis

An a-priori power analysis has been conducted using G*Power (version 3.1.9.6). We expect to find small, but relevant effects and therefore used an effect size of *f* = 0.14 for power calculation (*f*^2^ = 0.02). We intend to achieve a power of 1 – β = 0.95 and used a Bonferroni-adjusted α-level of α_adjusted_ = 0.05/3 = 0.017 (see data preparation and statistical analysis). With these parameters a total sample size of *N* = 174 (29 per condition) is needed for an analysis of variance for repeated measurements (rmANOVA) with six measurement time points and six conditions. Based on our experience with similar studies, we expect a small drop-out rate of about 10% due to insufficient saliva or blood volumes and will, therefore, recruit additional 18 participants (3 per condition). This results in a total sample size of *N* = 192.

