### Data preparation and statistical analysis

For statistical analysis, IBM SPSS Statistics (version 26 or higher for Windows) will be used. Data will be screened for outliers, and outliers which differ more than 3 standard deviations from the participants’ mean will be excluded from further analysis. Test of normality will be conducted by means of the Kolmogorov-Smirnov test. If necessary, data will be transformed (e.g., by means of the natural logarithm or square root transformation) to achieve a normality distribution.

For main hypotheses testing (research questions 1, 2, and 3), rmANOVAs will be conducted. In the analyses, the between-subjects factor ‘Condition’ (with six levels, see above) as well as the within-subjects factor ‘Time’ (with either six levels (for sAA, cortisol, and ECG measures), two for CRP and IL-6, and two for s-IgA) will be included. Three separate analyses will be conducted, one for SNS and PNS markers (i.e., sAA, HR, and RMSSD) and six measurement time points (s_1_ to s_6_), one for cortisol as the only HPA-axis marker with the same six time points, and one for the immune parameters (i.e., IL-6, CRP, and s-IgA) and two measurement time points. An additional factor ‘Measure’ (e.g., with the levels IL-6, CRP, and s-IgA for immune parameters) will be included if necessary. A Bonferroni-adjusted α-level of α_adjusted_ = 0.05/3 = 0.017 will be used for the main analyses, because three separate rmANOVAs will be conducted. The potential confounders age, sex, BMI, use of oral contraceptives and menstrual cycle phase for female participants, as well as time of day will be included in all statistical analyses as covariates.

Research question 4 (i.e., perceived stress, state anxiety, and affect) will be investigated analogously to research questions 1 to 3 by means of a further rmANOVA. The same α_adjusted_ = 0.017 as for main hypothesis testing will be used. For analysis of research question 5 (i.e., associations with person characteristics and psychological variables), nominal scaled variables (e.g., sex and education) will be included as additional factors in further rmANOVAs. For metric variables, multivariate regression analyses will be conducted in which the potential moderator variables will be included as moderator variables. For these analyses, the SPSS macro PROCESS [102] will be used. For these analyses which refer to research question 5, an adjusted α-level of α_adjusted_ = 0.001 will be used.

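### The only power calculation is for a six-time-point rmANOVA, but it sizes all three confirmatory analyses, and the immune analysis has two time points and probably less than 0.95 power if f = 0.14 carries over.

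*Protocol article*

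**What the plan says.** The section Power analysis in the protocol article sets the target ("We intend to achieve a power of 1 – β = 0.95") and the significance level ("used a Bonferroni-adjusted α-level of α_adjusted_ = 0.05/3 = 0.017"), with an effect size of f = 0.14. It concludes that "a total sample size of *N* = 174 (29 per condition) is needed". The design to which that number belongs is given in the same sentence: it "is needed for an analysis of variance for repeated measurements (rmANOVA) with six measurement time points and six conditions". Eighteen participants are added for a loss of about 10%, giving 192. The section does not say which effect is powered (interaction or main effect), what correlation among repeated measures was entered, or what nonsphericity value was used.

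The section Data preparation and statistical analysis plans three separate rmANOVAs at the adjusted alpha: SNS/PNS markers at six times, cortisol at six times, and immune parameters at two times. The levels of the time factor for the immune markers are "two for CRP and IL-6, and two for s-IgA". The section Primary outcomes includes CRP, IL-6 and s-IgA, and both main hypotheses predict an immune response.

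**The concern.** In repeated-measures power calculations of this kind, the number of time points enters the noncentrality directly. At a fixed f, fewer time points mean less power. A sample size found for six times therefore does not carry its 0.95 over to an analysis with two.

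The alpha in the calculation is the one shared by the three confirmatory analyses, and the resulting N is the only one given. A reader will naturally take 0.95 as the power of each. A null immune result could then be read as strong evidence against an effect of f = 0.14 when the chance of missing it may have been well above 5%.

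**Working it through.** **Inputs.** From the article: k = 6 conditions, f = 0.14 (f² = 0.0196), alpha = 0.05/3, N = 174 analysable and 192 recruited, m = 6 times for sAA, ECG measures and cortisol, m = 2 for the immune analysis. Assumed because not stated: the effect is Condition x Time, and r and epsilon take the values shown.

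**Formula** (noncentral F for the within-between interaction in the G*Power convention):
- lambda = f² · N · m · eps / (1 − r)
- df1 = (k − 1)(m − 1) · eps
- df2 = (N − k)(m − 1) · eps

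**Step 1: reproduce N = 174.** With m = 6, r = 0.5, eps = 1:
- lambda = 0.0196 × 174 × 6 / 0.5 = 40.92; df1 = 25; df2 = 840; power = 0.954.
- The smallest N is 172, which rounds up to 174 for equal groups. At 168 (28 per condition) power is 0.944.
- At r = 0.5 and eps = 1, the within-subject main effect (N = 108) and the between-subject main effect (N = 720) do not give 174.

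**Step 2: are r and epsilon identified?** No. These pairs also give 174 with six times:

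| r | eps | six-time power at 174 | two-time power at 174 |
|---|---|---|---|
| 0.5 | 1 | 0.954 | 0.67 |
| 0.6 | about 0.70 | 0.950 | 0.80 |
| 0.7 | about 0.47 | 0.954 | 0.92 |
| 0.75 | about 0.36 | 0.952 | 0.97 |

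**Step 3: immune analysis, f held at 0.14.** With m = 2 and r = 0.5:
- lambda = 0.0196 × 174 × 2 / 0.5 = 13.64; df1 = 5; df2 = 168; power = 0.67.
- With all 192 analysable: lambda = 15.05, power = 0.73.
- Other correlations at N = 174: 0.48 at r = 0.3, 0.80 at r = 0.6, 0.92 at r = 0.7. Power reaches 0.95 at r of about 0.73.
- With three times (CRP and IL-6 are sampled three times in Table 2): lambda = 20.46, df1 = 10, df2 = 336, power = 0.78 at r = 0.5.
- Effect detectable with 0.95 power at m = 2, N = 174, r = 0.5: f of about 0.19.

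Epsilon plays no part in the two-time analysis, because sphericity cannot fail with two levels.

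**Step 4: six-time analyses if eps = 1 was entered.** At N = 174 and r = 0.5, power is 0.89 at eps = 0.75 (lambda = 30.69) and 0.74 at eps = 0.5 (lambda = 20.46).

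**Step 5: does f = 0.14 mean the same effect at two and six times?** Suppose, as an illustration, that conditions differ at one time point only. The interaction variance is then proportional to (1/m)(1 − 1/m), which is 5/36 for m = 6 and 1/4 for m = 2. The ratio is 1.8, so the raw response behind f = 0.14 at six times is f = 0.14 × √1.8 = 0.188 at two. Then lambda = 0.0196 × 1.8 × 174 × 2 / 0.5 = 24.55 and power = 0.946 (0.968 at N = 192).

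**The case against.** Three points on the other side have weight.

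- **The settings are inferred.** A reader might infer that the 0.95 was computed under perfect sphericity and that immune power is simply 0.68. The article does not support either statement. The software's output can be matched with r = 0.5 and eps = 1, but also with pairs that already allow for nonsphericity. In those cases two-time power is higher, and at r = 0.75 with eps about 0.36 it passes 0.95. This objection stands, and the figure must be given as a range over r.
- **Holding f constant is a convention.** Step 5 shows that a response confined to one time point gives a larger f with two times and almost restores 0.95. The article expects IL-6 and s-IgA to peak at +90 minutes, so a baseline-to-peak contrast is plausible for them. A more spread-out response would give another figure. This also stands. However, the article states one f and does not say that a larger one is expected for the immune markers.
- **The article does not literally claim 0.95 for the immune analysis.** It ties N = 174 to six time points, and that arithmetic is correct. A reader might call this a calculation error, and it is not one. The defect is that one of three confirmatory analyses is sized by a calculation for a different design.

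The actual immune model is also unsettled: an additional Measure factor is included only if necessary, covariates enter, and Table 2 lists three CRP and IL-6 samples where the analysis uses two. Its exact power cannot be computed from the article. At r = 0.5 and f = 0.14, even three times leave power at about 0.78.

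**Conclusion.** The point holds in a limited form. The stated N reproduces for a six-time Condition x Time interaction, but no power is given for the two-time immune analysis, although it is confirmatory and shares the same alpha. If f = 0.14 carries over, its power at N = 174 is about 0.67 at r = 0.5, rising to 0.80 at r = 0.6 and 0.92 at r = 0.7. It meets 0.95 only if r exceeds about 0.73, which the article nowhere assumes. With r = 0.5 and all 192 analysable, it is 0.73.

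The result rests on two assumptions: the value of r, and an f that is the same at two times as at six. If the second is relaxed to a response at a single time point, power at r = 0.5 is close to 0.95. So the article does not establish 0.95 for the immune analysis, but it does not establish a fixed shortfall either. The lower six-time figures apply only if eps = 1 was in fact entered.

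**What to change.** In Power analysis:

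1. Name Condition x Time as the powered effect, and state the r and epsilon actually entered.
2. Give power, or the effect detectable with 0.95 power, separately for the six-time analyses and for the immune analysis. For the latter, state the r and the f assumed at two times and show a range over r. At r = 0.5 and N = 174 this would read about 0.67 for f = 0.14, or a detectable f of about 0.19.
3. If epsilon = 1 was used, add the six-time power at lower values (about 0.89 at 0.75 and 0.74 at 0.5, for r = 0.5).
4. Do not claim 0.95 for the immune analysis unless the stated r and f support it.
5. Settle whether CRP and IL-6 enter with two or three times, and compute the immune figure for that number.

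The cost is a few sentences and possibly a less favourable figure for one analysis. The design, the planned analyses and the number of participants stay as they are.

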### Experimental setting and procedure

After providing informed and written consent, participants will be equipped with the heart rate monitors and will be familiarized with the saliva collection procedure via Salivettes (i.e., the collection of the stimulated saliva samples), and a practice saliva sample (s_0_) will be collected, which will not be used for later analyses. After this, all participants–irrespective of the actual group assignment–will conduct practice trials of the VFT and the CPT and will be informed that they will possibly have to repeat these tasks throughout the session. This will be followed by a resting period of about 20 minutes. At the end of the resting period, the first blood spot sample (DBS_1_) and the next stimulated saliva sample (s_1_) as well as the first unstimulated saliva sample (us_1_) will be collected. After this, the main task will be introduced to the participants and will then start immediately and will last about 21 minutes. Introduction of the task and the actual task will take a total of about 25 minutes. Immediately after the end of the main task, participants will provide the second saliva sample (s_2_; i.e., end of the main task +0 minutes). The subsequent stimulated saliva samples will be collected at the following time points: +10 (s_3_), +20 (s_4_), +45 (s_5_), and +90 (s_6_) minutes after the end of the main task. The second Dried Blood Spot (DBS_2_) as well as the second unstimulated saliva sample (us_2_) will also be collected at + 90 minutes post task. During the time window between the task and the last saliva and blood sample, participants will rest and will fill out questionnaires until the end of the session and will be allowed to take as many breaks as they prefer. The goal of this period is not to stress the participants while conducting a non-stressful task (i.e., filling-out the questionnaires). The timeline of the whole experiment is shown in Fig 3. The entire session will last about 3 hours. Additionally, participants will provide another blood sample (DBS_3_) 24 hours after the first one. This DBS collection will be conducted by the participants themselves at their homes and samples will be send back via mail.

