### Potential risks

From a practical point of view, there is a risk that the blood and saliva volumes will be too low for analysis. However, this has been included in the sample size-calculation and will be minimized by training the experimenters by experienced researchers. A further potential risk is that the recruitment goal might not be fulfilled, e.g., due to the Covid-19 pandemic. In the case that another lockdown will be imposed, recruitment will be paused.

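### The planned rmANOVA drops a participant from an analysis for one missing value, and the 10% allowance leaves no reserve for losses other than insufficient sample volume

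*Protocol article*

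**What the plan says.** The section Data preparation and statistical analysis names SPSS and plans three rmANOVAs, each with Condition (six levels) between subjects and Time within subjects:

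- the autonomic analysis, described as "one for SNS and PNS markers (i.e., sAA, HR, and RMSSD) and six measurement time points";
- cortisol, at the same six time points;
- the immune markers, at two time points.

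A further factor, Measure, is to be added where necessary. The alpha level is divided by three "because three separate rmANOVAs will be conducted". The same section excludes values more than 3 SD from the mean.

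The Power analysis section sizes the trial at 174 for six groups and six time points, then adds 18 people because "we expect a small drop-out rate of about 10% due to insufficient saliva or blood volumes". The section Potential risks repeats that "there is a risk that the blood and saliva volumes will be too low for analysis", says that this was allowed for in the sample size, and adds that experimenters will be trained to limit it. Neither section mentions any other cause of missing values, and no analysis that keeps partly observed participants is named.

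**The concern.** A low-volume sample is a missing value, not a missing person. The plan equates the two because its chosen analysis does: a classical rmANOVA, including the repeated-measures procedure in SPSS, needs a full row of repeated values and deletes any participant who lacks one.

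The stimulated saliva samples supply both sAA and cortisol. A sample at +45 minutes that is too small for both assays removes that person from two of the three main tests, although five of the six samples are good. If sAA, HR and RMSSD are modelled together, the person's ECG values leave the autonomic test as well.

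Two things are at stake: data already collected and paid for are not used, and the number analysed falls below the planned figure as soon as any value is lost for a reason other than volume.

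**Working it through.** **Inputs from the Power analysis section.** f = 0.14 (f² = 0.0196), alpha = 0.017, target power 0.95, six conditions, six time points, N = 174, 18 added, total 192.

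**Assumed, because the article does not state them.** Correlation between repeated measures r = 0.5 and sphericity epsilon = 1. Losses are independent. The per-value loss rates below are illustrations.

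**1. The plan's own figures.** For the Condition × Time test:

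- λ = f² × N × 6 / (1 − r)
- df1 = 5 × 5 = 25, df2 = 5 × (N − 6)

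At N = 174, λ = 0.0196 × 174 × 6 / 0.5 = 40.9 and df2 = 840, which gives power 0.955. One participant fewer per condition (N = 168) gives 0.945. So 174 is the smallest balanced size that reaches 0.95, and the stated N reproduces. The total follows from 174 × 1.10 = 191.4, rounded to 192.

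**2. What the allowance leaves.** 192 × 0.90 = 172.8 completers, power 0.953. The target is met, but the expected number is already just under 174. The added 18 are 18/192 = 9.4% of those recruited.

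**3. How per-sample failure becomes participant loss.** With six required saliva samples and failure rate q per sample, the share lost is 1 − (1 − q)^6. The 18 are used up when 1 − q = (174/192)^(1/6), that is q = 1.63%.

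| q per sample | Lost | Completers of 192 | Power |
|---|---|---|---|
| 1% | 5.9% | 181 | above 0.955 |
| 2% | 11.4% | 170 | 0.95 |
| 3% | 16.7% | 160 | 0.93 |
| 5% | 26.5% | 141 | 0.87 |

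Failures that cluster within a person would cost fewer participants than this.

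**4. Adding a loss that the allowance does not name.** Start from 172.8 and apply the 3 SD exclusion at the normal-theory rate of 0.27% of values:

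- Cortisol, 6 values per person: 172.8 × 0.9973^6 = 172.8 × 0.984 = 170.0; power 0.948.
- Joint sAA/HR/RMSSD, 3 × 6 = 18 values per person: 172.8 × 0.9973^18 = 172.8 × 0.952 = 164.6; power 0.938.
- The same joint model with 1% of values lost, to outliers, unusable ECG or early leaving together: 172.8 × 0.99^18 = 172.8 × 0.835 = 144.2; power about 0.88.

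The power figures for the joint model are those of a single-marker Condition × Time test at the reduced N. They show the effect of the smaller sample, not the exact power of a three-marker model.

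The outlier rule is read here as distance from the mean across participants. If it meant distance from a person's own mean of six values, nothing could be excluded: with the usual sample SD, the largest possible distance is (6 − 1)/√6 = 2.04 SD. Under that reading only the other causes of loss remain.

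**The case against.** The best case for the plan has four parts.

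- **The three analyses are separate.** A failed blood spot leaves sAA, ECG and cortisol untouched, and a failed stimulated sample leaves the immune analysis untouched. ECG values are lost through a saliva failure only under joint modelling, and the Measure factor is conditional. This stands. A reader might infer that one bad sample deletes a participant's whole record; the article does not support that.
- **The 10% is a participant-level rate based on the team's experience.** It may already be the share of people with any insufficient sample, in which case power holds at about 0.953. Training and a practice saliva sample should also limit failures. This stands too. That the allowance will easily be exceeded cannot be shown from the article, which gives no failure rate per sample or for the ECG.
- **Selection bias is not evidenced.** One might argue that strong responders produce less saliva and so drop out more often. Nothing in the article links sample volume to condition or response.
- **The home sample is not a route to loss.** The article says of the 24-hour sample: "This DBS collection will be conducted by the participants themselves at their homes and samples will be send back via mail". A reader might count unreturned cards as lost participants. But the immune analysis is fixed at two time points and s-IgA is measured only at baseline and +90 minutes, so no planned two-time-point immune model is shown to need the 24-hour value.

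It can also be said that missing-data handling belongs in an analysis plan that is not shown. That would answer a complaint about silence. It does not answer this one, because the article itself fixes the rmANOVA and counts insufficient samples as drop-out.

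**Conclusion.** The point holds within each analysis. The chosen rmANOVA discards the valid repeated values of any participant with one missing value in that analysis, and the allowance covers insufficient volume only.

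If the 10% is right and nothing else is lost, the stated power is kept. With small further losses it slips to about 0.95 for cortisol and 0.94 for a joint autonomic model, and to about 0.88 if 1% of the joint model's values are lost. These sizes rest on r = 0.5, epsilon = 1, independence and assumed loss rates. This is an avoidable inefficiency with no reserve behind it. It does not show that the trial is underpowered or its contrasts biased.

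**What to change.** In Data preparation and statistical analysis, replace the rmANOVA by a linear mixed model for repeated measures (MIXED in SPSS) with Condition, Time, their interaction and the covariates already listed. Fit it to all randomised participants with all available values, and report the number of missing samples by condition and time point.

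No participants, samples or new software are needed. According to Status and timeline of the study, analysis starts only after all data are collected and no preliminary analyses are planned, so the change can be made before any result is seen.

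The cost is slightly more analysis work, including the choice of a covariance structure, and reliance on data being missing at random. If failure depended on the unobserved response itself, the mixed model would not remove the resulting bias; the counts by condition would help readers judge whether that is a worry.
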